**Fig. 3 Fig3:**
[figure not shown]
Study power for comparing HIV incidence between post-DREAMS and pre-DREAMS time periods in (**a**) uMkhanyakude, South Africa and (**b**) Gem, Kenya

The same sample sizes will also allow us to detect meaningful change in secondary outcomes that are more common among AGYW than HIV incidence, including knowledge of HIV status and use of condoms (Additional file 1: Table S2). Secondary outcomes will also be measured at the population level for men including the proportion of males who know their HIV status, uptake of voluntary male medical circumcision among HIV-negative males, and uptake of anti-retroviral therapy among HIV-positive males (Additional file 1: Table S3).

For the nested cohorts in the three HDSS sites, selected from the HDSS sampling frames in South Africa and Western Kenya, a minimum of 400 girls in each of the 13–17 and 18–22 year age groups will allow us to analyze causal relationships between key mediators and key outcomes (Additional file 1: Table S4), and similarly to analyze causal relationships between uptake of DREAMS interventions and key outcomes. Over-sampling by 20% will cater for non-response and loss-to-follow-up. In Nairobi, for the additional cohort of 400 younger girls aged 10–14), the sample size of 400 will allow us to explore pathways between uptake of DREAMS interventions, key mediators and age-appropriate outcomes like school completion.

In Zimbabwe, network-based recruitment will be used to enroll 18 to 24-year-old women who sell sex from intervention and comparison sites. Based on the assumption that 20% of YWSS identified through this process will test HIV-positive and 30% of HIV-negative YWSS will be lost to follow-up over 24 months, it is estimated that 1200 women from the intervention and comparison sites (2400 total) will be needed to detect a 40% reduction in HIV incidence [8]. This sample size is also sufficient to explore pathways linking DREAMS to secondary outcomes.

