**Methods:**

To achieve an impact evaluation that is credible and timely, we describe a mix of methods that build on longitudinal data available in existing surveillance sites prior to DREAMS roll-out. In three long-running surveillance sites (in rural and urban Kenya and rural South Africa), the evaluation will measure: (1) population-level changes over time in HIV incidence and socio-economic, behavioural and health outcomes among AGYW and young men (before, during, after DREAMS); and (2) causal pathways linking uptake of DREAMS interventions to ‘mediators’ of change such as empowerment, through to behavioural and health outcomes, using nested cohort studies with samples of ~ 1000–1500 AGYW selected randomly from the general population and followed for two years. In Zimbabwe, where DREAMS includes an offer of pre-exposure HIV prophylaxis (PrEP), cohorts of young women who sell sex will be followed for two years to measure the impact of ‘DREAMS+PrEP’ on HIV incidence among young women at highest risk of HIV. In all four settings, process evaluation and qualitative studies will monitor the delivery and context of DREAMS implementation. The primary evaluation outcome is HIV incidence, and secondary outcomes include indicators of sexual behavior change, and social and biological protection.

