To achieve the above, the design comprises three main components:**Population-based surveillance systems**: In uMkhanyakude, and Gem and Nairobi in Kenya, existing surveillance systems that link HIV, demographic, behavioural, and service uptake data, will be used and enhanced in order to assess the population-level effects of DREAMS over time (in relation to the timing of DREAMS roll-out) among AGYW, men who are in the age range that includes most of the partners of AGYW, and also older adults who may receive DREAMS interventions that are directed at the wider community. In uMkhanyakude and Gem, linkage to HIV clinic data is possible and geospatial data are available, and in uMkhanyakude HIV phylogenetics data are also available. We will utilise historical (for baseline) and prospective data (for comparison) from the population-based systems (see Fig. 2 for example in South Africa).**Cohorts of AGYW**, randomly selected from the total population: For detailed study of the pathways by which DREAMS interventions influence HIV risk, we will establish cohorts of AGYW within each evaluation site. Cohort enrolment will be completed during the early roll-out of DREAMS interventions, during 2017, and those enrolled will be followed prospectively, at ~ 12 and ~ 24 months later. There will be more detailed and comprehensive data collection on uptake of DREAMS interventions, mediators of change, and socio-economic, behavioural and health outcomes than is possible in the total population. In the Zimbabwe setting, the same cohort used to measure the overall impact of DREAMS interventions on HIV incidence among YWSS can be used to analyse pathways of change.In uMkhanyakude, Nairobi, and Gem, nested cohorts of AGYW aged 13–22 will be selected using the HDSS census population as the sampling frame. A random sample of AGYW stratified by age (13–17 and 18–22 years) and area of residence will be selected. The Nairobi evaluation will further recruit a sample of young girls from age 10 (building on the Global Early Adolescent Study pilot in this setting), resulting in three age groups for the cohorts: 10–14, 15–17, and 18–22 years.

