#### Analysis of causal pathways

To explore whether the hypothesized “mediators of change” lie on the causal pathway between the DREAMS interventions and HIV-related (secondary) outcomes (Table 2), longitudinal data collected from the nested AGYW cohorts at three time points over two years will be used (enrolment; 12 months; 24 months). The causal analysis will involve four main steps:Analysis of whether uptake of DREAMS interventions is related to an improvement in the “mediators of change”, between enrolment and follow-up at 12 and 24 monthsAnalysis of whether uptake of DREAMS interventions is related to “lower-risk” sexual behaviour, social protections, and biological protections, at follow-up at 12 and 24 monthsAnalysis of whether improved levels of the “mediators of change” are related to “lower-risk” sexual behavior, social protections, and biological protections, at enrolment and during follow-upCausal mediation analysis of the effect of DREAMS interventions on secondary outcomes (biological, behavioral, social), i.e., the extent to which any effect of DREAMS interventions on secondary outcomes after 12 and 24 months of follow-up is achieved through their effect on the “mediating” variables.

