#### Sample sizes

HIV incidence - the primary endpoint for the impact evaluation - will be measured using HDSS data in uMkhanyakude and Gem, and data from the cohorts of young women who sell sex in Zimbabwe. In uMkhanyakude, HIV incidence was ~ 6 per 100 person-years among AGYW aged 15–24 years old during 2011–2015, and ~ 4.6 and ~ 7.5 per 100 person-years among those aged 15–19 and 20–24 years respectively, based on a total of 7687 person-years of follow-up. Assuming, conservatively, that there will be ~ 3000 person-years of follow-up during 2017–2019 (40% of 7687), [20] then study power is > 90% to show an overall reduction in HIV incidence of 30, and > 90% in sub-group analysis of AGYW aged 15–19 and 20–24 years to show a 40% reduction in HIV incidence (Fig. 3a). In Gem, western Kenya, HIV incidence was ~ 0.7 per 100 person-years among AGYW aged 15–24 years during 2011–2016, based on a total of 8236 person-years of follow-up [21]. (Whereas sero-surveys are conducted annually in uMkhanyakude, they are less frequent in Gem: data are available from three sero-surveys in Gem between 2011 and 2016. Sero-conversions observed during this period, including those estimated from the 2016 survey, will be considered ‘pre-DREAMS’ because they are unlikely to be influenced by DREAMS by this early stage of implementation.) During 2017–2019, all AGYW in Gem will be sought for participation in the HDSS; with a participation rate of 70% in each year, and an annual out-migration rate of 20%, it is estimated that there will be ~ 9000 person-years of follow-up during 2016–2019. Study power is low to show a change in HIV incidence in sub-group analyses of AGYW aged 15–19 and 20–24 years, but ~ 80% to show an overall reduction of 45, and 90% to show an overall reduction of 50% in HIV incidence (Fig. 3b).

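### At Gem, 20% over-sampling of the nested cohort does not cover non-response plus two years of loss at the rates the protocol assumes for the same surveillance population

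*Protocol article*

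**What the plan says.** All places are in the protocol article.

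- **Sample sizes, nested-cohort paragraph after Figure 3:** for the cohorts in the three surveillance sites, "a minimum of 400 girls in each of the 13–17 and 18–22 year age groups will allow us to analyze causal relationships" between mediators, uptake and outcomes. The next sentence reads "Over-sampling by 20% will cater for non-response and loss-to-follow-up". One allowance therefore has to absorb both kinds of loss.
- **Sample sizes, opening paragraph:** the Gem person-years for 2017–2019 are projected "with a participation rate of 70% in each year, and an annual out-migration rate of 20" per cent.
- **Study design, cohort component:** the "nested cohorts of AGYW aged 13–22 will be selected using the HDSS census population as the sampling frame". Enrolment is to be complete during 2017, and "those enrolled will be followed prospectively, at ~ 12 and ~ 24 months later".
- **Analysis of causal pathways:** "longitudinal data collected from the nested AGYW cohorts at three time points over two years will be used (enrolment; 12 months; 24 months").
- **Abstract, Methods:** the cohorts are described as "nested cohort studies with samples of ~ 1000–1500 AGYW selected randomly from the general population and followed for two years".

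The article gives no response or retention rate specific to the nested cohorts at any of the three sites.

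**The concern.** The over-sampling sentence is an unqualified claim of sufficiency, and the same section contains rates against which it can be tested at one site. The Gem cohort comes from the Gem surveillance population, is enrolled in 2017 and is followed for two years, which is the period for which the participation and out-migration rates were assumed. If those rates are realistic for planning the incidence analysis, they are the natural starting point for the cohort too, and a 20% allowance looks too small.

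What is at stake is the number of girls per age group who contribute 24-month data to the uptake, mediator and mediation analyses. If that number falls well below 400, these analyses are less precise than the text implies. They are also to be adjusted for a propensity score in 4–5 categories plus individual confounders, so there is little slack. The primary outcome is not affected: Table 3 assigns no primary outcome to these cohorts, because HIV incidence comes from the larger population-level data.

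**Working it through.** **Inputs.** Minimum per age group: 400. Over-sampling: 20%. Gem participation: 70% per year. Gem out-migration: 20% per year. Follow-up: two years. Cohort size per site: about 1000–1500.

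**Step 1. Number sampled per age group.** There are two readings of the allowance.

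- 400 × 1.2 = 480, which gives 2 × 480 = 960 and 3 × 480 = 1440.
- 400 / (1 − 0.20) = 500, which gives 2 × 500 = 1000 and 3 × 500 = 1500.

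The second reading reproduces the abstract's range exactly: two age groups at the lower end, and the three Nairobi age groups at the upper end. The first is 4% below. Both are carried through.

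**Step 2. Loss the allowance tolerates.** 1 − 400/480 = 16.7%; 1 − 400/500 = 20%.

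**Step 3. Number left at the Gem rates.** Number left = sampled × response × (1 − annual out-migration)^years. Number to sample to keep 400 = 400 / proportion left.

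| Loss applied | Proportion left | From 480 | From 500 | Sample needed to keep 400 |
|---|---|---|---|---|
| Out-migration, one year | 0.80 | 384 | 400 | 500 |
| Out-migration, two years | 0.80² = 0.64 | 307 | 320 | 625 |
| Non-response only | 0.70 | 336 | 350 | 572 |
| Non-response and two years of out-migration | 0.70 × 0.64 = 0.448 | 215 | 224 | 893 |

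Each Gem rate alone exceeds the allowance over two years, so the conclusion does not depend on multiplying them. One year of out-migration by itself uses up the whole allowance. The 70% is applied once only, not compounded over the three survey rounds.

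**Step 4. What would have to be true for 20% to suffice.** With full response, the largest annual loss covered is 1 − √(400/480) = 8.7%, or 1 − √(400/500) = 10.6%. With 10% non-response (my assumption, for illustration), it is 1 − √(0.8333/0.9) = 3.8%, or 1 − √(0.8/0.9) = 5.7%. The assumed Gem out-migration is 20%.

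**Step 5. Effect on precision.** Standard errors scale with √(400/n).

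- Two years of out-migration: √(400/307) = 1.14, or √(400/320) = 1.12.
- Both losses: √(400/215) = 1.36, or √(400/224) = 1.34.

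Intervals would thus be about 12–14% or 34–36% wider than at 400.

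**The case against.** The strongest objection is that the Gem rates were not stated for the nested cohort. They are inputs to a person-years projection in which all adolescent girls and young women in Gem are sought, and the incidence outcome concerns ages 15–24, whereas the cohort is an individually sampled group aged 13–22. Annual surveillance participation is not the same as enrolment non-response, and tracing out-migrants or replacing non-responders could reduce losses. Site-specific protocols are available on request and may contain such arrangements. All of this stands as a limit on the result: the cohort losses at Gem are not known from the article. It does not remove the conflict. These are the only rates given for the source population and period, the article mentions neither tracing nor replacement, and its claim that 20% is enough is a positive statement with nothing behind it.

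A second objection is that 400 might be needed only at enrolment, since part of the pathway analysis uses enrolment and 12-month data. But an allowance meant to cover loss to follow-up implies a number left afterwards. Even at enrolment, 70% response would give 336–350.

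A third is that Gem might sample more. Taking 1500 in two groups (750 each) would leave 480 after two years of out-migration alone, but 750 × 0.448 = 336 after both losses. The 1500 in any case fits three Nairobi groups of 500.

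Three stronger readings are tempting and are not supported:

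- **That the minimum fails at all three sites.** uMkhanyakude and Nairobi have their own surveillance populations, and no participation or migration rates are given for them.
- **That the Zimbabwe assumption proves the point.** There the plan supposes that "30% of HIV-negative YWSS will be lost to follow-up over 24 months", but this concerns a hidden population recruited through networks without a sampling frame. It says nothing about retention of girls sampled from a census.
- **That the detectable effects in Additional file 1, Table S4 are too optimistic.** That table is not shown, so neither its basis nor its power at 400 can be checked.

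**Conclusion.** The point holds for Gem. A 20% allowance tolerates 16.7–20% combined loss, and either of the rates assumed for the Gem surveillance population breaks it over two years. From 480–500 sampled per age group, about 307–320 would remain after out-migration alone, 336–350 after non-response alone, and 215–224 after both, against a stated minimum of 400.

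This rests on three assumptions: that the surveillance rates carry over to the cohort, that out-migrants are lost to follow-up, and that non-responders are not replaced. For uMkhanyakude and Nairobi the allowance is unsupported, not shown to fail. The correction should be made, but its weight is moderate, because these cohorts serve the secondary pathway analyses.

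**What to change.** Replace the over-sampling sentence with, for each site's cohort, the assumed response, the assumed 24-month retention and the resulting expected number per age group, computed as sampled n × response × retention. If an inflation factor is kept, derive it as 400 / (response × retention).

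For Gem, do one of two things. Either use the participation and out-migration rates already in Sample sizes, which give about 215–320 per group at 24 months depending on which losses apply, or state why cohort losses will be lower, for example through tracing of migrants or replacement of non-responders.

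If the detectable effects in Table S4 were computed at 400 with 24-month data, restate them at the expected numbers.

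The cost is revised text and possibly one revised table. No extra recruitment is required. The downside is a less favourable stated precision for the pathway analyses.

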## Discussion

DREAMS is a direct response – probably the most ambitious yet – to the call for combinations or ‘packages’ of prevention approaches to address the multidimensional nature of HIV risk. PEPFAR and its DREAMS partners have set bold targets and allocated significant resources to urgently reduce new HIV infections. It is important to learn from these efforts, but evaluating such a multi-component programme is complex.

In the first instance, a randomised design was not possible because DREAMS sites were not selected at random, but chosen for their high burden of HIV prevalence and incidence. Furthermore, interventions in the core package cannot be rolled out at random, as implementation will begin with the interventions already in place (e.g., through pre-existing PEPFAR and national government programmes) and this is context-specific. Neither was a controlled design possible, given the numerous differences (non-comparability) across sub-national geographic units, as well as the absence of existing surveillance/data platforms in other areas, to allow for comparable data collection.

We have proposed the most rigorous design feasible in the absence of randomisation. Community-wide data platforms allow us to evaluate DREAMS in large, general populations, and provide the frameworks for randomly selected, representative samples of young people for detailed, nested studies. The range of data available (HIV, demographic, social, spatial, clinical) can be linked to maximize the range and depth of inquiry. In all settings, detailed longitudinal data will allow us to investigate pathways and explore change processes in the context of DREAMS roll-out (and minimize recall and reporting bias), and to account for a range of potential confounding variables. Historical measures of HIV incidence and other outcomes will provide baseline trend data, to help distinguish the impact of DREAMS from existing trends due to other factors.

In this study, estimates of HIV incidence will be directly observed through repeat testing and can be compared to levels of newly diagnosed infections in pregnant women tested in antenatal clinics serving the study populations, since the latter is a method by which PEPFAR will assess programme impact in DREAMS sites (e.g., through monitoring of ante-natal care testing data as part of Prevention of Mother to Child Transmission programmes) [22]. Tracking new HIV diagnoses can be a helpful complement to incidence rates, offering insight into the reach and yield of HIV testing services.

A particular challenge of this evaluation is also one of its main strengths: harmonizing across diverse settings. Each setting presents unique opportunities to deepen the understanding of AGYW’s experience of DREAMS, but coordinating the design and measures across settings is not always possible. For example, in Nairobi, we have an opportunity to understand DREAMS impact in an urban setting and to capitalize on the site’s extensive experience with young people, to track pathways through DREAMS from a very young age. In this setting, however, we will not be able to observe change in HIV incidence (except indirectly, by monitoring antenatal clinic outcomes of HIV testing). Gem offers a rural comparison to Nairobi, where we can measure the added value of DREAMS following wide-scale roll-out of anti-retroviral therapy and VMMC. In uMkhanyakude, we have an opportunity to evaluate DREAMS in a setting where HIV risk has remained persistently high and relatively few HIV prevention interventions have targeted AGYW prior to DREAMS. In Zimbabwe, no HDSS framework exists, but we will gain insight into the DREAMS+PrEP package, and understand HIV and HIV-related outcomes among an exceptionally vulnerable group of young women.

Working with existing research platforms offers infrastructure, experience and data prior to DREAMS introduction. However, it also means that data collection cannot be conducted at the same time in each site, and this must be taken into account in analyses and interpretation. Also, community sensitisation efforts are planned in each site to avoid research fatigue and maximize data quality and validity in settings with frequent and/or concurrent surveys. Furthermore, in each setting, DREAMS is delivered through different models of collaboration and implementation, and changes in implementation will occur in each setting over time. This heterogeneity and its influence on outcomes will need to be understood through careful process evaluation.

With a portfolio of evaluations in diverse settings, the sum can be greater than its parts. Learning within and across sites, we can document the role of context and adaptation in DREAMS impact, to inform replication in a range of other diverse settings. The effectiveness of the individual interventions in the DREAMS core package have been demonstrated in previous trials and evaluations. We now need to understand how they can be combined for maximum reach, scale and impact. This evaluation will investigate this in ‘real-world’, non-trial conditions, providing immediately relevant and timely lessons for future policy and programming.

## Abbreviations

AGYW: Adolescent girls and young women
AHRI: Africa Health Research Institute
APHRC: African Population and Health Research Center
ART: Anti-retroviral therapy
CDC: United States Centers for Disease Control and Prevention
CeSHHAR: Centre for Sexual Health and HIV AIDS Research
DREAMS: Determined, Resilient, Empowered, AIDS-free, Mentored, Safe lives
FGD: Focus group discussion
FSW: Female sex workers
GEAS: Global Early Adolescent Study
HDSS: Health and demographic surveillance system
HIV: Human immunodeficiency virus
HSV-2: Herpes simplex virus type 2
HTC: HIV testing and counselling
HTS: HIV testing services
IE: Impact Evaluation
IP: Implementing Partner for DREAMS
KEMRI: Kenya Medical Research Institute
KP_Prev: Number of key populations reached with HIV prevention interventions
KZN: KwaZulu-Natal
LSHTM: London School of Hygiene & Tropical Medicine
LSTM: Liverpool School of Tropical Medicine
NHLS: National Health Laboratory Services
PEP: Post-exposure prophylaxis (for HIV)
PEPFAR: The United States President’s Emergency Plan for AIDS Relief
PrEP: Pre-exposure prophylaxis (for HIV)
SRH: Sexual and reproductive health
STI: Sexually transmitted infection
UK: United Kingdom
US: United States
VMMC: Voluntary male medical circumcision
YWSS: Young women who sell sex
